#### Analysis plan

The sessions will be audio recorded, transcribed using NVivo, and analyzed using rapid qualitative analysis [54]. Rapid qualitative analysis will allow the research team to balance rigor of analysis with the need to rapidly synthesize data within sessions to inform each subsequent session. The process will include validity checks through independent coding by multiple members. Key insights will inform the refinement of implementation strategies, with all processes adhering to ethical guidelines to maintain confidentiality for participant contributions.

#### Output: implementation strategy package

Implementation strategies are defined as methods or techniques used to facilitate the adoption, implementation, and sustainability of a clinical program or practice, including provider training and decision support, intervention-specific tool kits, checklists, formal practice protocols and guidelines, and economic, fiscal, and regulatory strategies [51, 53]. For each selected implementation strategy, we will define and operationalize each implementation strategy needed to address multilevel barriers by describing the actors, action, targets of the action, temporality, doses, and implementation outcomes [53]. An example of implementation strategy is shown in Fig. 3. We anticipate finalizing up to three care-setting-specific strategy scenarios for simulation testing in Aim 3.

**Fig. 3 Fig3:**
[figure not shown]
A hypothetical example of implementation strategy in an ED setting

### Aim 3 – Simulation modeling via agent-based modeling

#### Study design

The objective of Aim 3 is to develop and apply an agent-based model (ABM) to simulate HIV transmission, healthcare engagement, and the effect(s) of hypothetical implementation strategies on key health outcomes among people with OUD in Rhode Island. The model will project outcomes over 5- and 10-year horizons, assessing the potential reach and effectiveness of tailored implementation approaches, identified in Aim 2, prior to real-world piloting.

#### Model framework

The ABM will simulate a “virtual society” of people in Rhode Island with OUD, representing dynamic, heterogeneous agents interacting through injecting and/or sexual networks. The model will build upon the TITAN model (prior open-source simulation developed by [name] team), and incorporate healthcare-seeking behaviors across various care settings (ED, primary care clinic, substance use treatment center, and mental health clinic), and interactions between provider agents and OUD patient agents during HIV prevention care [55]. The final model will be implemented in Python™, and managed by a trained research programmer with ABM expertise. Our model will operate in discrete (monthly) time steps, with stochastic transitions between states and interactions governed by empirically derived probabilities. The model will simulate the delivery of HIV prevention and MOUD services within care settings and assess how implementation strategies modify these probabilities to influence health outcomes (e.g., HIV incidence trajectories) in Rhode Island.

#### Model input

Model parameters will be drawn from three sources: administrative data from Aim 1 (e.g., healthcare usage patterns by demographic subgroup), stakeholder-derived strategy components from Aim 2 (e.g., settings and delivery mechanisms for HIV prevention services), and published literature on HIV natural history and behavioral dynamics. A repository of parameter values, assumptions, and data sources will be created to guide calibration and facilitate reproducibility.

Agents will have attributes that evolve over time, and allow for bidirectional interactions between agents and their environment. At each discrete time step, agents will be connected to each other in a population-based contact network. Network edges (representing relationships) will be formed, retained, or broken over the lifetime of the simulation, representing partnership acquisition and dissolution in a dynamic contact network. This network of interactions will represent the primary pathway(s) for HIV transmission within the agent population. Examples of model parameters are listed in Table 2.

**Table 2 Tab2:** Example parameters in agent-based models to assess effectiveness of intervention package(s)

**Patient-level**
Acceptance of rapid HIV testing, PrEP, and MOUD Possibility of HIV-negative results Chance of being interested in PrEP and MOUD Possibility of PrEP and MOUD eligible Chance of receiving a PrEP/MOUD prescription Possibility of picking up PrEP/MOUD Estimated time on PrEP/MOUD Possibility of seeking care in EDs, primary care, mental health, and substance use centers Patterns of key SDH
**Provider-level**
Chance of receiving PrEP/MOUD education and training Possibility of receiving a certificate for a PrEP/MOUD prescription Chance of conducting HIV and PrEP counseling and MOUD assessment Possibility of conducting a PrEP/MOUD evaluation Chance of prescribing PrEP/MOUD Possibility of referring for follow-up visits
**System-level**
Chance of funding to support HIV prevention services and MOUD Effectiveness of care coordination between care settings

At model initialization, “agents” of people with OUD will be randomly assigned endogenous traits based on information collected during Aim 1 and the literature.^37^ These discrete state variables include demographics (age, sex, race, ethnicity), risk behavior profiles (injection and non-injection drug use, sexual risk behavior), clinical characteristics (HIV status, PrEP use, MOUD status, healthcare usage), and key SDHs (housing, incarceration, insurance status, employment, sex work involvement). Agents representing people with OUD will be subject to a probability of death due to opioid overdose, HIV-related diseases, or other causes that will be impacted by their gender, drug use status, incarceration status, and the usage of healthcare in general. Meanwhile, agents representing healthcare providers will also be randomly assigned endogenous characteristics including: demographics, role (e.g., nurse, physician, clinical coordinator), attitudes towards HIV and OUD, knowledge (of HIV, PrEP, MOUD), and previous history of PrEP prescription. Agents representing healthcare providers will be subject to the probability of stopping their medical practice in the selected care setting due to retirement, resignation, and death.

The simulation will also include a set of environmental parameters/variables (e.g., how clinics, labs, and pharmacies are connected geographically or operationally) and the availability of resources (e.g., staffing capacity, pharmacy access, and laboratory infrastructure). These environmental factors will influence access to care, delays in treatment, and referral patterns, and are critical to accurately modeling real-world constraints in health service delivery.

#### Outcome definition

The base model will represent the status quo—current levels of HIV prevention service delivery across different care settings, as established through Aim 1. Using Python™, we will evaluate the effect of each proposed implementation strategy (developed in Aim 2) on multiple outcome measures over 5- and 10-year projections.

Key outcomes will include projected HIV incidence across the population, as well as the number of new HIV cases averted or caused relative to the base model. We will also assess changes in healthcare utilization patterns and quantify uptake of PrEP and MOUD by setting. For each intervention scenario, we will calculate the number needed to treat (NNT)—defined as the number of HIV prevention service encounters or MOUD prescriptions required to prevent a single HIV infection over a specified time horizon. And lastly, the model will assess the population-level impact of integrating HIV prevention services into OUD care. These outcomes will guide the selection of the most effective and feasible strategy package for real-world implementation and inform the prioritization of approaches for future pilot testing and scale-up.

#### Model calibration and validation

Model calibration will follow a multi-step approach. First, we will create a repository of context-specific parameters, documenting data sources, values, and their temporal variability. This parameter repository will facilitate identification of input uncertainty and guide systematic model development. Next, we will evaluate the robustness of simulation outcomes under varying assumptions through a structured stress test of three rule sets: (1) a core rule set, based on strong empirical evidence; (2) an expanded rule set, incorporating additional but less well-supported behavioral and structural processes; and (3) a randomized rule set, intended to assess the effects of confounding or unanticipated dynamics.

After defining the rule sets, we will calibrate the model using Approximate Bayesian Computation (ABC) to reproduce observed historical trends, including HIV incidence and outcomes derived in Aim 1 such as ED utilization among people with OUD. Model outputs will be validated by comparing simulated and empirical HIV incidence trends in Rhode Island using Euclidean distance metrics. Calibration will be iteratively refined until model outputs closely match observed data. Because the model includes numerous stochastic components, all simulations will employ Markov Chain Monte Carlo methods to produce robust distributions of outcome estimates. For each rule set, the model will be executed 1,000 times to estimate central tendencies and variances. All simulations will be run on a high-performance computing cluster to ensure computational efficiency and scalability.

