## Background

An estimated 2.7 million people have opioid use disorder (OUD) in the United States (US), and more than 105,000 overdose deaths occurred in 2023 [1]. As the opioid overdose epidemic has worsened, there has been growing concern about opioid use fueling the transmission of infectious diseases, including HIV and hepatitis C virus. An estimated 2.6% of the US population has a history of injection drug use, further underscoring the importance of studying links between OUD and HIV [2]. Opioid use has been associated with several HIV outbreaks in the US since 2015, and approximately 2300 new HIV infections were due to injection drug use in 2022 [3–6]. Despite the availability of effective HIV prevention and intervention strategies, many people with OUD do not receive these strategies in the places where they receive care, highlighting a pressing implementation gap [7].

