#### Data sources

We will use two primary data sources to capture insured and uninsured individuals in RI:Rhode Island (RI) All-Payer Claims Database (APCD) includes longitudinal medical and pharmacy claims, participant demographics and enrollment information, and provider characteristics data from private insurers, Medicare, and Medicaid (Table 1). APCD data are updated monthly and reflect over 90% of the insured population in RI (based on our preliminary analysis). We will use APCD data between 2012 and 2022 to evaluate trends over time.Rhode Island State Emergency Department Database (SEDD): Captures encounter-level data for ED visits, including those involving uninsured individuals (estimated 5.0% of RI population, based on 2022 data) [48]. While SEDD lacks unique patient identifiers and pharmacy/provider details, it complements APCD by providing a more complete picture of ED utilization among patients who may be excluded from claims-based analyses. Because SEDD does not allow for longitudinal tracking of individuals across visits, these data will be used to characterize encounter-level trends among the uninsured population. APCD and SEDD will not be linked at the individual level; however, each will be analyzed separately but interpreted together to capture utilization across the full population of people with OUD.

**Table 1 Tab1:** Data variables for statistical analysis in Aim 1

Demographic data	Medical care information	Provider information
Age Sex ZIP Code City Insurance information Relationship to health policyholder Internal unique identifier	Date of service Type of service Location of service Date prescription(s) filled ICD-9/10 diagnostic codes National Drug Code Prescription refill indicator Pharmacy ID Inpatient and outpatient claims Mental health claims	Practice Attending provider name Prescribing provider name Type Primary care indicator Specialty Address ZIP Code City Pharmacy ID

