### Anticipated contributions

Our approach addresses critical gaps in the integration of HIV prevention services within systems that serve people with OUD. While the public health urgency of the HIV/OUD syndemic is well-established, real-world implementation of evidence-based interventions among people with OUD remains limited. This study offers several key contributions: (1) a comprehensive analysis of insured (APCD) and uninsured (SEDD) data to identify missed opportunities for HIV prevention; (2) use of an EBQI process to co-design strategies with healthcare providers, policymakers, and individuals with lived experience; and (3) application of ABM to test and predict impact of implementation scenarios. Each aim builds upon one another, producing a validated, context-specific final strategy that is ready for real-world implementation.

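### If yearly HIV counts are small, validating the base model by Euclidean distance has low power against a one-directional bias; signed checks on the total and the slope would detect it more often

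*Protocol article*

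**What the plan says.** Under Model calibration and validation (Aim 3), the article first plans to "calibrate the model using Approximate Bayesian Computation (ABC) to reproduce observed historical trends, including HIV incidence and outcomes derived in Aim 1". It then names the validation method: "Model outputs will be validated by comparing simulated and empirical HIV incidence trends in Rhode Island using Euclidean distance metrics". The stopping rule is verbal: "Calibration will be iteratively refined until model outputs closely match observed data". On replication it says: "For each rule set, the model will be executed 1,000 times to estimate central tendencies and variances".

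Under Outcome definition, cases averted or caused are counted relative to the base model, and NNT is computed for each intervention scenario. Under Anticipated contributions, the three aims together are described as "producing a validated, context-specific final strategy that is ready for real-world implementation".

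No Rhode Island HIV count is given. The only related figure is national, in the Background: "approximately 2300 new HIV infections were due to injection drug use in 2022". The article does not say whether the validation series covers the whole state or only people with OUD, nor which years it spans.

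**The concern.** A Euclidean distance sums squared yearly differences. A model that is too high every year and a model that scatters evenly around the data can score alike, because sign plays no part and a consistent excess is never accumulated. Nor does the distance account for count variance. When yearly counts are small, Poisson scatter makes up most of the distance and can hide a systematic excess.

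The level of the base model is at stake. To first order, cases averted scale with base incidence, so a uniform 30% excess inflates them by about 30%. NNT is divided by the same factor: 1/1.3 = 0.77, about 23% too low. The planned one-way and multi-way sensitivity analyses vary the inputs; they do not test whether the base model's level agrees with the data.

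**Working it through.** The article states no count, threshold or error rate for validation, so there is no figure of its own to reproduce. The check below is conditional.

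**Inputs**
- Metric: Euclidean distance between simulated and observed yearly incidence (article).
- Years: T = 11, an assumption borrowed from the Aim 1 claims window ("We will use APCD data between 2012 and 2022 to evaluate trends over time"). The window of the HIV series is not stated.
- Yearly cases: λ = 5 to 20, an assumption. For orientation only, an assumed state share of 0.2–0.5% of the national 2300 gives 2300 × 0.002 = 4.6 to 2300 × 0.005 = 11.5 injection-related cases a year.
- Observed counts: Poisson(λ). The model is represented by its mean trajectory, since averaging 1,000 runs leaves little Monte Carlo noise.
- Bias: the model mean is 1.3λ in every year, chosen for illustration.
- Cut-off: 5%, an assumption, set in two ways: (a) from the biased model's own predictive distribution, (b) from the distance distribution of a correct model.

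**Why power is low.** The expected squared distance is Tλ for a correct model and T(λ + 0.09λ²) for the biased one. At λ = 7 these are 11 × 7 = 77 and 11 × (7 + 4.41) = 125.5. Judged by its own predictive distribution, the biased model expects T × 1.3λ = 100.1, so its larger expected noise absorbs about half of the gap. The signed total behaves differently. The model expects 100.1 cases and 77 are expected in truth. The gap of 23.1 is about 2.3 standard deviations of the model's total (√100.1 ≈ 10.0).

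**Probability of rejecting the model that is 30% too high (11 years)**

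| Cases a year | Euclidean, cut-off (a) | Euclidean, cut-off (b) | Cumulative count |
|---|---|---|---|
| 5 | 4% | 21% | 48% |
| 7 | 10% | 34% | 66% |
| 10 | 22% | 52% | 82% |
| 15 | 47% | 75% | 94% |
| 20 | 68% | 89% | 98% |
| 30 | 92% | 98% | over 99% |

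The Euclidean columns are simulated. The last column is an exact Poisson calculation using the lower 2.5% tail of the model's total.

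**Further results**
- Asymmetry: at 7 a year, cut-off (a) rejects a model 30% too low 64% of the time but one 30% too high only 10%. That rule is lenient towards overstated incidence.
- Shape: against a true threefold decline (1.5 to 0.5 times the mean), a flat model at 7 a year is rejected about 37% of the time by distance under cut-off (a) and about 78% by a slope check.
- A Poisson deviance alone, in place of the distance, reaches only about 29% at 7 a year. Most of the gain comes from the signed checks.
- Shorter series: over 5 years under cut-off (b), the biased model passes 86% of the time at 5 a year, 68% at 10 and 36% at 20.
- Very small counts: at 3 a year over 11 years, even the cumulative check has only 34% power.

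**The case against.** A reader might infer that the metric cannot distinguish a right model from one 30% too high, and that a badly biased model will be declared validated. The documents do not support that.
- No pass rule is stated, so no verdict follows from the text. The two cut-offs are assumptions, and at 7 a year they differ threefold (10% against 34%).
- The correct model is usually the closer one: in about 90% of data sets at 7 a year and 94% at 10.

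Nor would the weakness remain whatever data are used. The validation sentence speaks of Rhode Island trends, the model includes sexual as well as injecting networks, and the series may be statewide. At 50 a year over 11 years, even the more lenient rule rejects the biased model 99.8% of the time.

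The strongest counter-argument is calibration. ABC fits incidence before validation. If the model had one free constant level, the best-fitting level would be the mean yearly count, which would be 30% or more too high in only about 0.5% of data sets at 7 a year. That stands as a reason why so large a bias is less likely. It is not a test: the agent-based model must also meet other targets, such as ED utilization, and its structure limits what it can fit.

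A uniform excess also need not change the ranking of strategies. That too stands, but cases averted and NNT are themselves named outcomes. Finally, tolerances and the exact series may sit in a fuller modelling plan, so their absence from an article is not the point here. The choice of metric is stated in the article and can be judged.

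**Conclusion.** The point holds in a limited, conditional form. The stated metric ignores sign and count noise. At an assumed 5 to 20 cases a year over 11 years, it detects a 30% overstatement less often than a cumulative count does, under either cut-off. The difference is large at 5 to 10 a year (4–52% against 48–82%), modest at 20 (68–89% against 98%) and small from 30 upward.

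This rests on the assumed counts, the Poisson model, 11 yearly points, a fixed mean trajectory and a 5% rule that the article does not contain. Overdispersion or parameter uncertainty in the predictive distribution would lower the power of every check. What the documents support is a worthwhile, inexpensive improvement to a stated method; they do not show that validation will fail.

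**What to change.** In Model calibration and validation:

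1. Name the validation series, its years and its yearly counts.
2. Keep a distance measure, or use a Poisson or negative-binomial discrepancy for the yearly counts. The discrepancy alone is not enough.
3. Add two signed posterior-predictive checks, set before calibration: cumulative cases over the period and the slope over time. For each, require the observed value to lie inside the 95% predictive interval.
4. Report the relative bias in cumulative incidence with its interval, and carry that uncertainty into the intervals for cases averted and NNT.
5. If counts are very small (about 3 a year), state that a bias of about 30% cannot be excluded.

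The cost is a few sentences of protocol wording and a few lines of code, with no new data. The downside is that the model may fail the stricter check and need revision.

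### As described, the agent-based model is validated against HIV incidence, a series it is calibrated to, so the check is goodness of fit and does not support calling the final strategy validated and ready for implementation

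*Protocol article*

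**What the plan says.** The relevant text is in the protocol article, mainly under Aim 3, Model calibration and validation. Three statements follow one another there:

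- Calibration: "we will calibrate the model using Approximate Bayesian Computation (ABC) to reproduce observed historical trends, including HIV incidence and outcomes derived in Aim 1". Emergency department use is the example given of an Aim 1 outcome.
- Validation: "Model outputs will be validated by comparing simulated and empirical HIV incidence trends in Rhode Island using Euclidean distance metrics".
- Refinement: "Calibration will be iteratively refined until model outputs closely match observed data".

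Under Model framework, the simulated population is "people in Rhode Island with OUD, representing dynamic, heterogeneous agents interacting through injecting and/or sexual networks".

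Under Outcome definition, "Key outcomes will include projected HIV incidence across the population", together with cases averted relative to the base model, over 5 and 10 years. On their use: "These outcomes will guide the selection of the most effective and feasible strategy package for real-world implementation".

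In the Discussion, Anticipated contributions, the three aims together are described as "producing a validated, context-specific final strategy that is ready for real-world implementation".

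**The concern.** Validation should show how well a model predicts data that played no part in fitting it. Here the series used to judge the model is also one used to fit it, and fitting goes on until agreement is close. A small distance between simulated and observed incidence is then the point at which tuning stops. It tells the reader that the model can be made to follow the past, but not how far its projections may be wrong.

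The projected quantity, HIV incidence, is the same quantity again, and the projections decide which strategy package goes forward. A reader of the final report who sees the word validated would reasonably assume that forecast error had been examined on independent data. The described procedure would not have done so.

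**Working it through.** The article attaches no threshold, fit statistic or sample size to this step, so there is no figure to reproduce. The check sets the statements side by side.

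1. **Calibration targets.** HIV incidence and Aim 1 outcomes.
2. **Validation target.** HIV incidence trends in Rhode Island. No other validation quantity is named. The calibration sentence does not repeat the state's name, but the article names no other incidence series, and the model represents people with opioid use disorder in that state.
3. **Overlap.** The validation target lies inside the set of calibration targets. No split of years, separate data source or unfitted outcome is stated. The Aim 1 study window is 2012 to 2022, and nothing divides it into fitting and testing years.
4. **Consequence of a poor match.** Calibration is refined. No outcome is described in which the model is recorded as having failed.
5. **Other checks that might fill the gap.** The stress test of three rule sets and the one-way and multi-way sensitivity analyses vary assumptions. The 1,000 runs per rule set describe stochastic spread. None compares the model with data it was not fitted to.
6. **What the claim needs.** The Discussion applies validated to the strategy. Even a good forecast of status-quo incidence would test the base model only. It would not test the simulated effect of strategies that have never been implemented.

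**How sharp a held-out test could be.** This bears on the remedy only; the finding does not depend on it. The documents give no Rhode Island case count. For illustration, assume the state carries its population share (1.1 of 333 million, an assumption) of the roughly 2,300 injection-related infections in the Background: 2,300 × 1.1/333 = 7.6 a year, with 3 to 12 as an assumed range. Assume also a four-year hold-out and Poisson counts, and ignore posterior spread. The test accepts if the observed count lies between the 2.5% and 97.5% Poisson quantiles at the model's mean.

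- *Each year separately, all four required.* At 7.6 a year the interval is 3 to 13. A model with the right mean passes with probability 0.9575⁴ = 0.84, so it fails 16% of the time. If true incidence is 25% above the model (9.5 a year), it passes with probability 0.894⁴ = 0.64.
- *Four years pooled.* The model mean is 4 × 7.6 = 30.4 and the interval is 20 to 42. A right model fails about 4% of the time. With true incidence 25% above the model it still passes 77% of the time (87% at 3 a year, 63% at 12). With true incidence double the model it passes under 1% of the time (18% at 3 a year, under 0.1% at 12).

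Pooling controls false failure, and what it can detect is large misfit.

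**The case against.** The strongest reply is that this is a condensed article. It gives no years for either step, so a fuller plan may hold a temporal split. That stands, and it rules out saying that the model will have had no validation or that its forecast error will never be measured. It does not remove the point: the article has a section on this step and states targets, metric and refinement rule, and the procedure as stated is circular.

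A reader might also infer that agreement is guaranteed. The documents do not support that. The model must fit several targets jointly, with inputs taken from claims and literature, so it could fail to match. What holds is narrower: a mismatch is answered by further calibration, so a final match is not independent evidence.

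Two further inferences go beyond the text. One is that incidence for the whole state population will be forced onto a model of people with opioid use disorder. The reference to Rhode Island gives geography and does not say that the series covers everyone. The other is that an unscaled distance with no tolerance will be used. The article does not say so, and scaling and tolerance are details commonly left to a fuller plan.

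Finally, the document elsewhere speaks of piloting after the model, does not include implementation in this study, and measures cases averted against the base model, so some absolute error is shared between scenarios. This softens the practical consequence. It also shows that the wording in Anticipated contributions is out of line with the rest of the article.

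**Conclusion.** The point holds in this form: the validation described is goodness of fit to a calibration target. It gives no information on out-of-sample error for the 5- and 10-year projections, and it does not support calling the final strategy validated and ready for implementation.

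No numerical size can be given. The documents contain neither the incidence series nor a fit criterion, and the circularity does not depend on any count. The conclusion assumes that the incidence series named for validation is the one named for calibration, which is the natural reading because no other is mentioned. It does not assert that independent validation is absent from any unseen plan.

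This should be fixed. It falls short of a fatal flaw, because the study itself stops at simulation and the article foresees piloting before use.

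**What to change.** Before calibration begins:

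- Reserve data that will not enter the Approximate Bayesian Computation: a later block of years, compared as a pooled total over the block, or an Aim 1 outcome left out of the calibration targets, or both.
- State that the incidence series covers the same population as the agents, that is, people with opioid use disorder.
- Set the acceptance criterion in advance and allow for sampling error in the observed counts.
- Freeze the model, compare once without refitting, and report the result even if it fails.

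If no data can be reserved, rename the step goodness of fit. In either case, change Anticipated contributions so that the product is a strategy for pilot testing. That agrees with the Aim 3 Study design, Outcome definition and Implementation barriers sections, all of which place piloting after the simulation.

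The cost is some protocol wording and a division of the data before fitting. Fewer data remain for calibration, so the posterior will be wider. With few cases the held-out comparison will detect only large misfit, as the illustration under the working shows, and the report should say so. A pass would support the base model, not the effects of untried strategies.
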